### Individual counseling by the psychologist

Psychological counseling will be based on the Rational Emotive Behavioral Therapy and its central concept ABC [42]. According to this concept, emotional and behavioral consequences (C) are the result of beliefs (B) on activating events (A). The psychologist and the woman will collaboratively evaluate and restructure the woman's erroneous beliefs about the climacteric stage and her emotional resources, which refer to the ability to positively guide the emotions to achieve a better level of self-esteem and self-efficacy. The psychologist and the woman will define the number of consultations required in accordance to her individual needs and characteristics.

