5) Percentage of women who practice regular leisure time physical activity (PA), where regular was defined as moderate intensity if done for ≥150 minutes/week or vigorous intensity if done ≥75 minutes/week.

6) Percentage of women who practice a healthy diet, which included the daily consumption of fruits (3-4 servings), vegetables (4-5 servings), and dairy products (2-3 servings).

The covariates will be:

a) Women's general characteristics: Age, schooling, marital and employment status.

b) Smoking status and alcohol consumption. Smoking status will consider former and current smokers and will register the number of cigarettes actually smoked per day. Alcohol consumption will be classified as non-drinkers (never drink alcohol), occasional drinkers (drink rarely or less than once a week), moderate drinkers (from 1 to 14 drinks per week) and heavy drinkers (more than 14 drinks per week).

c) Nutritional status will be measured by body mass index (BMI) and classified into groups of normal weight (BMI of 18.5-24.9 kg/m^2^), overweight (BMI of 25.0 to 29.9 kg/m^2^), or obese (BMI ≥30.0 kg/m^2^).

d) Social support (SS) will be measured by applying the DUKE-UNC-11 questionnaire [46]. This questionnaire evaluates confidential SS (possibility of having people to communicate with) with a minimum score of 7 points (low confidential SS) and a maximum score of 35 points (high confidential SS); and affective SS (demonstration of love, affection, and empathy) with a minimum score of 4 (low affective SS) and a maximum score of 20 points (high affective SS).

e) Medical and reproductive history: Presence of chronic diseases, number of pregnancies and living children, and menopause (one year after the last menstrual period). Type of menopause will be classified as natural or surgical, age at onset of menopause; time elapsed since menopause, presence and type of climacteric symptoms, and number of visits with the family doctor or other health provider in the last three months. The severity of vasomotor symptoms and vaginal atrophy symptoms is classified using the criteria proposed by the Department of Health and Human Services Food and Drug Administration [47], which are based upon women's self-report, and define the symptoms as mild, moderate, or severe.

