f) Satisfaction with care received at the FMC will be measured with the general question of how satisfied are you with the care you have received at the clinic? The possible answers are very satisfied, satisfied, neither satisfied nor unsatisfied, unsatisfied, and very unsatisfied.

g) Women's self-esteem will be measured with the Rosenberg Self-Esteem Scale (EAR) [48,49]. It is a one-domain instrument that consists of 10 questions. The highest score is 30 (high self-esteem) and the lowest is 0 (low self-esteem).

h) Adherence to MAIMC will be defined when the woman attends at least 60% of the planned individual and group counseling sessions.

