### Statistical analysis

The women characteristics of each intervention and comparison groups will be compared by using the Chi-square test to ascertain whether the groups were equivalent.

The effects of intervention for categorical outcome variables (regular leisure time physical activity, healthy diet) will be measured by comparing the baseline and post-intervention evaluation stages for differences in these variables using Chi-square test. Absolute percentage differences and corresponding 95% confidence intervals will be calculated.

Scores for the HR-QoL on the WHQ23 scale, the self-efficacy on the PHS-ES scale, the empowerment on the short form scale, knowledge about the climacteric stage, and menopause and self-care-related activities will be calculated according to the scoring algorithms. Measures of central tendency and distribution will be examined for these variables at the different measurement periods. The differences in the baseline and post-intervention stages for outcome variables will be compared within each group, and differences between the groups will be compared using the differences-in-differences (D-in-D) estimator [52]. The generalized linear model (GLM) will be used to assess changes in the main outcome variable controlling for baseline measures and other study variables as covariates. The GLM methods allow for modeling the correlation of the repeated observations on the same subjects [53].

The p value <0.05 will be considered as statistically significant. The analysis will be performed with the Stata 11.0 statistical software (Stata 11.0, Stata Corp; College Station, TX).

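### The covariate list behind the adjusted HR-QoL model includes session adherence, which exists only after baseline and only in the intervention clinic, and the other covariates are not limited to baseline values

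*Protocol article*

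**What the plan says.** In the protocol article, Statistical analysis gives two between-group analyses of the score outcomes. The first is a differences-in-differences estimator, described without covariates. The second is a generalized linear model for the main outcome (HR-QoL on the WHQ23), "controlling for baseline measures and other study variables as covariates".

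Study variables introduces a list with "The covariates will be" and runs from a) to h). The items that matter here are:

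- e) climacteric symptoms, and "number of visits with the family doctor or other health provider in the last three months"
- f) "Satisfaction with care received at the FMC will be measured with the general question"
- g) "Women's self-esteem will be measured with the Rosenberg Self-Esteem Scale"
- h) "Adherence to MAIMC will be defined when the woman attends at least 60% of the planned individual and group counseling sessions" (MAIMC is not spelled out in the article; I read it as the care model)

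No time point is attached to the list. Data collection says that study variables are recorded at baseline, three months and six months. The Discussion gives the reason for regression adjustment: women in the two clinics may differ in their baseline characteristics.

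**The concern.** A covariate that the intervention can change is not a confounder of its effect. Holding it fixed can absorb part of the effect being estimated, or introduce bias if the covariate and the outcome share unmeasured causes.

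The covariate set matters more than usual here. Two clinics chosen for convenience are compared without randomisation, and the Discussion relies on regression to deal with differences between them. If the adjusted coefficient does not estimate the effect of the care model, the analysis meant to repair the design answers another question.

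Adherence is the clear case, because it cannot be anything but post-baseline. Self-esteem is a stated target of the psychologist's sessions ("to achieve a better level of self-esteem and self-efficacy") and a theme of the second group session. The three-month look-back for visits covers the intervention period when asked at month 3, and the study nurse refers women to the family doctor and psychologist. Symptoms overlap the somatic and vasomotor domains of the WHQ23. Satisfaction with clinic care could plausibly move under a new model of care.

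**Working it through.** The plan states no figure to reproduce on this point. The check is algebra for adherence, followed by illustrations.

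**Adherence: what the coefficient becomes.** Let G = 1 in the intervention clinic and A = 1 for an adherent woman. Control women have no planned sessions, so A is either undefined for them, in which case they drop out and no group effect can be estimated, or coded 0. The article does not say which. Take A = 0.

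Let e_A and e_N be the mean gains over control in adherent and non-adherent intervention women, and p the share adherent. Then:

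- Mean gain = e_A·A + e_N·(G − A) = e_N·G + (e_A − e_N)·A
- Without A in the model, the group coefficient is p·e_A + (1 − p)·e_N, the average effect
- With A in the model, the group coefficient is e_N
- Difference = p·(e_A − e_N)

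This treats adherence as unrelated to prognosis. If it is related, the second coefficient also carries the prognostic difference between non-adherent women and controls.

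**Illustration.** From Sample size: difference 10 points, SD 23.4, and 107 per group less 20% = 85.6, so 86 evaluable. Assumed, not in the article: p = 0.7 and a baseline–follow-up correlation of 0.5.

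| Scenario | e_A | e_N | Without A | With A |
|---|---|---|---|---|
| All benefit in adherers | 14.29 | 0 | 10.0 | 0 |
| Non-adherers gain half as much | 11.76 | 5.88 | 0.7×11.76 + 0.3×5.88 = 10.0 | 5.9 |
| Equal gain | 10 | 10 | 10.0 | 10.0 |

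Simulation of the first two rows (2,000 trials each) gave 9.9 falling to −0.1, and 10.1 falling to 6.0. The right-hand column simply returns the assumed e_N. It shows what is being estimated and does not predict a loss.

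**Precision.** Residual SD = 23.4 × √0.75 = 20.26.

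- Without A: 20.26 × √(2/86) = 3.1
- With A: 20.26 × √(1/25.8 + 1/86) = 4.5, since 0.3 × 86 = 25.8 women are non-adherent (simulated: 4.6)

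With equal groups, the correlation of G and A is 0.175/√(0.25 × 0.2275) = 0.73. The variance inflation is 1/(1 − 0.73²), about 2.2, and √2.2 is about 1.5.

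**The other four items: baseline or follow-up value.** Same sample size, true effect 10, one-sided 5% test. Assumed: the intervention shifts the covariate by 0.5 SD, and a given share of the effect passes through it.

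| Share through covariate | Baseline value in model | Follow-up value in model | Power, baseline → follow-up |
|---|---|---|---|
| 20% | 10.0 | 8.0 | 0.96 → 0.83 |
| 30% | 10.0 | 6.9 | 0.94 → 0.73 |
| 50% | 10.0 | 5.0 | 0.95 → 0.57 |

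The follow-up column is close to (1 − share) × 10, so again it reflects the assumption. With a 30% share and an unmeasured common cause of covariate and outcome, the follow-up coefficient was 5.0, not the direct effect of 7. The distortion is therefore not limited to removing the mediated part. Baseline values do no harm in any row.

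**The case against.** The strongest reply is that the list a) to h) is an inventory of non-outcome variables and not a model specification. The model sentence does not say which items enter or at which visit. The Discussion ties regression to baseline differences between clinics, which points to baseline values that the intervention cannot have altered. An article may leave the final covariate set to a fuller document. The differences-in-differences comparison is described without covariates, so a between-group estimate free of this problem would be reported in any case.

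Much of this stands for satisfaction, self-esteem, visits and symptoms. A reader might infer that the plan adjusts for their follow-up values. The text does not say so, and collecting a variable at three visits does not put every value into the model. A reader might also infer that the primary analysis is compromised, but the article does not name the generalized linear model as primary over differences-in-differences. Nor is adherence nearly collinear with group: at 70% adherence the correlation is 0.73.

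The reply does not rescue adherence. The article itself places it under the covariates, the model sentence draws on study variables as covariates, and nothing excludes it. It has no baseline value to fall back on.

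**Conclusion.** The point holds in two parts of unequal strength.

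For adherence it holds on the text. Followed as written, with controls coded as non-adherent, the adjusted HR-QoL model gives the contrast for non-adherent women. That change of estimand does not depend on the adherence rate. Its numerical effect does: with an average effect of 10 points and 70% adherence, the coefficient runs from 0 to 10 across the scenarios shown, and the standard error rises about 1.5-fold. The adherence rate, the split of benefit and the correlation of 0.5 are all assumptions. No single figure, such as a halved effect, can be drawn from the documents.

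For satisfaction, self-esteem, visits and symptoms, the plan permits but does not state adjustment for variables the intervention can change. If baseline values are used, as the Discussion makes plausible, no effect is lost. If follow-up values are used, bias is likely, usually but not always towards no effect.

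**What to change.** In Statistical analysis, remove adherence (item h) from the adjusted HR-QoL model. Use it only to describe delivery of the intervention or in a separate, labelled secondary analysis. State that all other covariates enter at their baseline values. Treat follow-up satisfaction and self-esteem as outcomes or mediators, not adjustment terms, and keep follow-up visits and symptoms out of the adjustment set.

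The cost is a few lines of wording. Data collection already provides for baseline recording of the study variables, so no new data, visits or participants are needed.

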## Methods/Design

A field trial with one intervention and one comparison group, with ex ante and ex post measurements will be conducted in two IMSS primary care clinics in Mexico City. The clinics will be selected for convenience; each clinic must have more than 20 family doctors' offices and available space for the intervention (consulting room and an area for group counseling) and should have accepted to participate in the study; The intervention will be conducted in one clinic and the other clinic will serve as a comparison group, where the usual care for climacteric stage women will be observed.

The study population will consist of women affiliated with IMSS, between 45 and 59 years of age with a maximum of 5 years after menopause. The women should be users of the clinic, and should not have mental conditions that would prevent them from understanding the information or from taking independent decisions (dementia, mental retardation or psychosis), a physical disability that would impede them from participating (hearing loss, diseases affecting physical mobility as severe forms of rheumatoid arthritis), medical diagnosis of depression, diabetes mellitus, hypertension, renal or liver failure, and/or cancer, because patients with these diseases require specific care provided by several specialists. All women must agree to participate in the study through written informed consent.

The project was authorized by the National Research and Ethics Committee of the IMSS.

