### Group counseling

All women of the intervention group will be invited to eight weekly, 90-minutes group sessions to facilitate and enhance their knowledge about menopause and their care, as well as to share experiences, concerns and motivations, with other women. Each group session will be coordinated by the nurse or psychologist of the study and will include five to ten women. The group sessions will focus on common educational needs. Both individual and group counseling will be supported by printed material developed *ex profeso*, which participants will be encouraged to keep as a source of information.

The main themes of group sessions will be: 1) the climacteric stage and the empowerment approach; 2) Emotional well-being, self-esteem and self-efficacy during menopause; 3) Factors that predispose chronic disease development during the climacteric stage and health-related self-care strategies; 4) Physical activity: barriers, benefits, type, frequency and recommended time. How to establish an individual action plan on physical activity and make it feasible (problem solving); 5) Healthy diet during the climacteric stage including increase of intake of fruits, vegetables and dairy products on a daily basis, as well as education about the barriers to and benefits of a healthy diet. How to establish an individual action plan toward a healthy diet and make it feasible; 6-8) Monitoring of the progress of women's action plans. Participants should attend to group sessions one to five, and to sessions six to eight can attend either as a group or individually.

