### Data collection

Information on the study variables will be collected on three occasions: when the woman enters to the study (baseline), once intervention is complete (at three months) and after three more months of follow-up (six months).

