### Sample size

The sample size for the primary outcome (HR-QoL) was estimated by using the formula to test change in the mean of two normally distributed samples in longitudinal studies [50]. An average increase of at least 10 points in one or more domains of WHQ23 in the intervention group compared with control group women was considered to be clinically relevant. The assumptions included: a mean HR-QoL score of 64.9 points (standard deviation of 23.4 points) in the domain of general well-being [51], α = 0.05 (for one-sided hypothesis) and β = 0.20. The number of women by group, assuming a drop-out rate of 20% will be 107.

We also estimated a sample size for regular leisure time physical activity considering that this is the outcome variable more difficult to achieve. It was assumed that only 17% of women in Mexico engaged in some type of regular leisure time physical activity [11] and a positive increase of at least 10% will be achieved after women participation in the IHCM. For this calculation, we used the formula to test the difference of proportions between two populations [50] with a = 0.05 (one side) and the power of 80%. The total number of women by group to include assuming a drop-out rate of 20% will be 207.

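### Intervention women are counselled in shared groups and control women are not, but the only correlation the analysis plans to model is within a woman

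*Protocol article*

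**What the plan says.** Under Data collection, "Information on the study variables will be collected on three occasions": baseline, three months and six months. For the continuous scores, the Statistical analysis section says that "differences between the groups will be compared using the differences-in-differences (D-in-D) estimator". It then sets out a covariate-adjusted model: "The generalized linear model (GLM) will be used to assess changes in the main outcome variable controlling for baseline measures and other study variables as" (quote cut one word before its end). On correlation it adds one sentence: "The GLM methods allow for modeling the correlation of the repeated observations on the same subjects".

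On delivery, the Group counseling section says: "All women of the intervention group will be invited to eight weekly, 90-minutes group sessions". It continues: "Each group session will be coordinated by the nurse or psychologist of the study and will include five to ten women". The control clinic gives usual care from the family doctor and the routine prevention programmes, and no counselling groups are described there. Neither the Sample size nor the Statistical analysis section mentions correlation between women who share a group.

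**The concern.** Women who sit together for up to eight sessions, with the same facilitator and the same group discussion, may change in similar ways. Their outcomes are then not independent given treatment. The groups exist in one arm only, so the design is partially nested: the variance of the intervention mean is inflated and that of the control mean is not. A model whose only correlation is within a woman counts each intervention woman as fully independent information. The standard error of the clinic contrast is then too small and the p-value too optimistic. The error favours finding an effect.

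The naming of the model adds to this. A plain generalized linear model has no within-subject correlation; GEE, mixed models or cluster-robust errors supply it. The article states the aim but not which of these will be used, so the unit of clustering is left open.

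**Working it through.** **Inputs from the document.** Target difference 10 points ("An average increase of at least 10 points in one or more domains of WHQ23 in the intervention group" relative to control), SD 23.4, alpha 0.05, power 80%, drop-out 20%, 107 women per group for quality of life, 207 per group for physical activity, counselling groups of 5 to 10.

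**Assumed inputs.** Counselling-group ICC 0.01 to 0.10, as the document gives none. Equal total variance in both arms.

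**The plan's own figure.** For two means, n = 2 × [SD × (z_alpha + z_beta) / 10]².
- Two-sided 5%: 2 × [23.4 × (1.960 + 0.842) / 10]² = 85.95, and 85.95 / 0.8 = 107.4. This matches 107.
- One-sided 5%, as the text states: 67.7, and 67.7 / 0.8 = 84.6, so 85. This does not match.
- One-sided on change scores, with variance 2 × SD² × (1 − rho): gives 107 if rho is about 0.37, but no rho is stated.

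On either route that reaches 107, there is no allowance for clustering.

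**Effect of ignoring counselling groups.** With group size m, the design effect in the intervention arm is DE = 1 + (m − 1) × ICC, and it is 1 in the control arm. The ratio of true to naive standard error is sqrt((1 + DE) / 2). The true size of a nominal 5% two-sided test is 2 × [1 − Phi(1.960 / ratio)]. Power is at 86 evaluable women per arm, where the naive standard error is 23.4 × sqrt(2/86) = 3.57.

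| m | ICC | DE | SE ratio | True size | Two-sided power, n = 86 |
|---|---|---|---|---|---|
| 5 | 0.01 | 1.04 | 1.010 | 5.2% | 79% |
| 5 | 0.05 | 1.20 | 1.049 | 6.2% | 76% |
| 5 | 0.10 | 1.40 | 1.095 | 7.4% | 73% |
| 10 | 0.01 | 1.09 | 1.022 | 5.5% | 78% |
| 10 | 0.05 | 1.45 | 1.107 | 7.7% | 72% |
| 10 | 0.10 | 1.90 | 1.204 | 10.4% | 64% |

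The power column is what a correctly sized test would have, against 80% without clustering. To restore it with equal arms, 107 becomes 107 × (1 + DE) / 2, that is 110 to 156 per group. If 207 per group are enrolled (about 166 evaluable), two-sided power for quality of life stays at 90% to 97%. The size column does not improve, because it depends on m and ICC and not on the number of women.

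**Where the group effect must enter.** Write each woman's change as follow-up minus baseline. A group effect g that is the same at every visit contributes g − g = 0, so it drops out of the difference-in-differences contrast. A group effect that arises after baseline contributes g and stays. Simulation agrees. With 8 women per group, a constant effect leaves the size of the change-score test at about 5%. An effect arising after baseline gives 6.1% to 8.5% for ICC 0.02 to 0.10, close to the formula's 5.8% and 9.2% for m = 8. The groups form after enrolment, so the second case is the relevant one.

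**The case against.** This is a condensed article, and the exact model form may be in a fuller plan. The nurse's counselling is individual, and sessions six to eight may be attended individually, so shared exposure may be weaker than eight sessions suggest. The ICC is assumed, and at 0.01 to 0.02 the effect is small. All of this is fair and limits the size of the point. What it does not answer is that the article says which correlation the model covers, and that correlation is only on the same subjects.

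A reader might infer three stronger things, none of which the document supports.

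- *That the three measurements are treated as independent, so the planned standard errors are simply wrong.* The sentence after the model is named says within-subject correlation can be modelled. The label is imprecise, but no independence analysis over time is planned.
- *That adjusting for baseline while also using difference-in-differences is an error because baseline enters twice.* The two are listed as separate analyses. Regressing change on baseline gives the same treatment estimate as adjusting the follow-up score for baseline. They can differ when unrandomised clinics differ at baseline, but which should lead is a trade-off between assumptions. The Discussion gives a reason for adjusting.
- *That clustering by family doctor can be quantified.* The statement that "each clinic must have more than 20 family doctors' offices" is a condition for choosing clinics, not a count of participating doctors. In the intervention clinic doctors join voluntarily. Women per doctor and the ICC are unknown, and a doctor effect stable over visits cancels from the change contrast.

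**Conclusion.** The point holds in a limited form. The stated analysis covers correlation within a woman but has no term for the counselling group, which exists in one arm only. If change clusters by group, the between-group standard error is too small by a factor of 1.01 to 1.20, and a nominal 5% two-sided test has a true size of about 5.2% to 10.4%. That range rests on assumed ICCs of 0.01 to 0.10, groups of 5 to 10, equal variances and an effect arising after baseline. At the low end it can be ignored; with groups of ten and an ICC of 0.05 or more it is material. Enrolling the larger sample protects power but not the type I error. With one clinic per arm, clinic and treatment remain fully confounded, and no correlation model changes that.

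**What to change.** Three changes to the analysis text and one to data capture:

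1. Name the model: a linear mixed model (or GEE with robust standard errors) with within-woman correlation across the three visits.
2. Add a partially nested counselling-group effect, in the intervention arm only, acting on the post-baseline visits: a group-by-visit term, or a group effect on change. An intercept constant over all visits would not do, because it cancels from the contrast of interest. With GEE, the cluster for the robust error should be the counselling group in the intervention arm and the woman in the control arm.
3. State a small-sample correction. With 86 evaluable women there would be about 86/10 = 9 to 86/5 = 17 groups.
4. Record the counselling-group identifier for each intervention woman while the groups are running, since it may not be recoverable later.

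The cost is one extra identifier, a few lines of analysis text and slightly wider intervals if group effects exist.
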